**Fig. 2 Fig2:**
[figure not shown]
Participants time line. Assessed for eligibility = Children aged 6 to 59 months who assessed for moderate acute malnutrition based on inclusion/exclusion criteria. Complete assessment = Completion of screening for moderate acute malnutrition. Confirm willingness to participate = be sure for the willingness of care givers of the subject to be included in the study / informed consent. Randomization = Process of randomizing the subjects/ children aged 6 to 59 months who assessed and claimed as moderately malnourished. Base line data collection = collection of data before starting food ration. Follow-up = Weekly as well as monthly anthropometric assessment and daily food ration. End line data collection = Collection of data after completion of the follow up. t = indicates time that the processes have done/completed

### Training

Data collectors will receive training about the objectives of the study, data collection systems, interview techniques, anthropometric measurements, feeding procedures and field procedures prior to the data collection. Each question found in the questionnaire will be discussed during training, in which trainers will develop common understandings.

Standardization of anthropometric measures will be maintained. If it is possible, the same assessors will be used for all assessments.

### Pretesting

Pretesting of the questionnaire will be conducted in places away from where the actual study will be conducted. For the pretesting, 16 pairs of children and caregivers, which is 5% of the total sample size, will be interviewed to check the accuracy of questions and to decide on the length of interviews. During pretesting, consistency in the interpretation of questions will be checked to identify any unclear items. After the evaluation of instruments, all proposed revisions will be done before administering in the actual study.

### Harms

The food ingredients used for formulating the supplement will be foods which are already being used in these communities and are safe for consumption. The participants will get supplementary food at no cost as the treatment for their malnutrition status. There might be minimal risk of allergic reaction. There might be risk while making interactions and spending time through the process.

### Auditing

The study is open for auditing by any concerned organization, either government or non-government.

### Protocol amendment

Communication will be done regarding the protocol modification with those important stakeholders (IRB/IEC and Sponsor).

### Dissemination of the result

The result of this study will be disseminated through Internal Seminars, Conference presentations using outreach and public engagement events. Regular reporting and communication to stakeholders will be done. It will also disseminate through Publications.

### Potential benefits

This project will be carried out in the kebeles (neighborhoods) found in Wolaita zone where there is no provision of a supplementary feeding program. The children participating in this study will get supplementary food for their malnutrition. The intervention will enhance recovery from MAM, and those recovered from MAM will be discharged and rejoin the community.

Children who may develop serious allergic reactions like difficulty in breathing, dizziness, weakness or any unusual signs will be referred for treatment. Such participants will be excluded from the trial. Children who are temporarily sick or do not feel well will be sent to the health facility for the treatment, and their measurements will be rescheduled for other days.

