### Data collection

Selected caregivers of children with MAM aged 6 to 59 months will be interviewed for collection of baseline data such as socio-demographic and economic status, dietary habits, child’s age, breastfeeding practices and history of child and maternal illness. The child’s weight will be noted using a seca weight scale to the nearest 0.1 kg. The data collectors will be sure that the scale is placed on a flat, hard, even surface and will weigh with minimal clothing.

Height will be recorded to the nearest 0.1 cm using a seca height scale for children aged 24 to 59 months. For children aged 6 to 23 months, length will be measured to the nearest 0.1 cm using a locally made wooden measuring board. Before starting height measurement, the data collectors will ensure that the height board is on level ground and the child is without shoes; the collector will kneel in order to get to the level of the child and will encourage the caregiver to help. For length, data collectors will measure the child lying down, being sure that the length board is placed on a flat and stable surface.

MUAC will be documented by non-stretchable standard United Nations Children’s Fund (UNICEF) plastic tape measures. The measurement will be taken half-way between the acromion and the olecranon processes, with the measuring tape fitting comfortably, but without making a depression in the upper arm. Weekly assessment of anthropometric measurement using MUAC will be done by the data collectors for intervention as well as control groups. On a monthly basis, data collectors will again collect anthropometrics using the MUAC, height or length board and weight scale which are identical equipment to that used at baseline. At the same time, they will observe for bilateral pitting edema. Based on the follow-up measurement of anthropometry children who developed sever acute malnutrition will be referred to SAM clinic.

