### Description of interventions and distribution of supplementary foods

After collecting baseline information, each child in the intervention group will be given local ingredient-based supplement of 100 g with 20 g of sugar. The ration will be distributed on a daily basis for 12 weeks. The LIBS is made from 30 g of pumpkin seed, 25 g of peanut grain, 20 g of amaranth grain, 15 g of flaxseed, 10 g of emmer wheat, 25.2 g of sugar and 8 ml of oil. This supplement yielded 698.5 kcal (22.6 g protein, 40.89 g fat and 60.05 g carbohydrate). Similarly, each child in the control group will be given the conventional supplement (CSB+) with the amount of 150 g flour/day with 16 ml of oil (763.98.4 kcal, 23.5 g protein and 25 g fat) on a daily basis for a period of 12 weeks. The subjects will be served with both supplements in the morning as a breakfast (Table 1).

**Table 1 Tab1:** Nutrient composition of the supplementary foods

Nutrient	100 g of LIBS with 25.2 g of sugar plus 8 ml oil	150 g of CSB+ with 16 ml of oil
Energy (kcl)	698.5	763.98
Protein (gm)	22.6	20.25
Fat (gm)	40.89	30.76
Iron (mg)	8.1	6
Zn (mg)	5.6	7.5
Calcium (mg)	100	195
Phosphorous (mg)	470.55	300
Potassium (mg)	666.14	600
Magnesium (mg)	394.7	107.75
Sodium (mg)	84.6	41.25
Folic acid (μg)	49.4	90

Note: Nutrient values for the LIBS ration were calculated by using the USDA food composition database and NutriSurvey software. Nutrient values for the CSB+ was adapted from Amegovu KA, Ogwok P, Ochola S, Yiga P, Musalima HJ, Mutenyo E. Formulation of sorghum-peanut blend using linear programming for treatment of moderate acute malnutrition in Uganda. J Food Chem and Nutr. 2013; 1(2):67–77

Abbreviations: *LIBS* Local ingredients based supplement, *USDA* United States Department of Agriculture and *CSB+* Corn soy blend plus

According to the guidelines for selective feeding, all children 6–59 months of age will receive the same amount of food [23]. During the intervention period, the food distributers will visit households daily to assist the caregivers in the preparation of porridge and feeding, to advise, assess and resolve difficulties with feeding. Besides, they will check for and quantify the amount of supplement consumed by the children.

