### Data analysis

All data collection sheets will be controlled by the field supervisors for completeness. EpiData version 3.1 will be used for all data entry. Two data clerks will enter data simultaneously to ensure data quality. Continuous data quality evaluation will be made through automatic consistency checks. Statistical significance is set at 5% for all analyses. Statistical analysis will be done using SPSS and STATA software for survival and hazard ratio. The probability of recovery rate will be predicted in Kaplan-Meier (log rank) curves of survival analysis. T-tests, analysis of variance (ANOVAs) and chi-square tests will be used to assess baseline characteristics. In accordance with recommendations for analyzing and reporting equivalence and non-inferiority trials, both intention-to-treat (ITT) and per protocol (PP) analyses will be done, and the 95% CI will be used to infer whichever variances are significant [24]. The ITT analyses will include all children enrolled in the study whereas the PP analyses will exclude children who lost to follow-up, refused and transferred out of the management programme but include children discharged as cured, died or non-cured.

Logistic regression will be used to test for interactions between the recovery rate and other variables. Mean recovery time and median recovery time, mean differences of MUAC and mean difference between WHZ scores will be computed to describe the magnitude of the difference between the two groups.

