### Outcome variables

The primary outcome measure of this study will be recovery rate. ‘Recovered’ will be defined as when a child attains a MUAC ≥12.5 cm and WHZ scores ≥ − 2, without bipedal edema. The secondary outcomes are the mean recovery time and average weight gain. Children who developed SAM during the study and/or persisted as moderately malnourished at the end of the 3-month follow-up will be considered to have failed the management for MAM.

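### Children with reactions are to be excluded from the trial after randomisation, which conflicts with an ITT set of all enrolled children and leaves them without an outcome

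*Protocol article*

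**What the plan says.** Four parts of the protocol article bear on who is counted.

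- **Potential benefits.** The trigger is set out first: "Children who may develop serious allergic reactions like difficulty in breathing, dizziness, weakness or any unusual signs will be referred for treatment". The consequence comes in the next sentence of that section: "Such participants will be excluded from the trial". The same paragraph treats temporarily sick children differently: they are sent for care and their measurements are rescheduled, so they stay in.
- **Data analysis.** For the first analysis set the rule is "The ITT analyses will include all children enrolled in the study". The per-protocol set rests on two lists. The list of removals reads: "the PP analyses will exclude children who lost to follow-up, refused and transferred out of the management programme". The list of those retained reads: "include children discharged as cured, died or non-cured". Neither per-protocol list names a child excluded for a reaction.
- **Outcome variables.** Recovery is defined by MUAC, WHZ and absence of oedema. Failure has two routes, the second judged when the 12 weeks are over: "Children who developed SAM during the study and/or persisted as moderately malnourished". A child excluded before then fits neither description.
- **Data collection.** On the basis of follow-up anthropometry, "children who developed sever acute malnutrition will be referred to SAM clinic".

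The legend of the trial profile (Fig. 1) has a category for randomised children who are discontinued, but does not say how they are analysed.

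**The concern.** Excluding a child from the trial normally means that measurement stops and the child leaves the analysis. Here it happens after randomisation, and the trigger is something the supplement itself can cause. The trigger is also broad: weakness or any unusual sign is a matter of judgement and could catch a child who is doing badly for nutritional reasons. Such a child is more likely than average to be a non-recoverer.

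In a non-inferiority trial with a 7-point margin, losing non-recoverers from the test arm raises its observed recovery rate and makes an inferior product look acceptable. Even if the ITT definition prevails and the child stays in the denominator, the analyst still needs an outcome for a child no longer measured, and the article supplies no rule. That choice would then be made once data are in.

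**Working it through.** **1. The two rules side by side.** Potential benefits removes a class of randomised children from the trial. Data analysis keeps every enrolled child in ITT. If the first governs, ITT is no longer all enrolled children. If the second governs, the child is in ITT without a measured endpoint. Either way something must be decided that the article does not decide.

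**2. How much removal could matter.** The article gives no removal rate, so there is no figure of its own to reproduce on this point. Inputs from Sample size calculation: recovery 60% on LIBS and 67% on CSB+, margin 7 points, 162 children per arm. From Data analysis: a 95% CI. (The 162 does not follow from those inputs, because 0.07 - (0.67 - 0.60) = 0. That is a separate matter; 162 is used here only as the number randomised per arm.)

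Assume a fraction x of LIBS children is removed, all of them non-recovered, and none from CSB+:

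- observed LIBS rate: p = 0.60 / (1 - x)
- observed difference: d = p - 0.67
- standard error: se = sqrt[ p(1 - p) / (162(1 - x)) + 0.67 × 0.33 / 162 ]
- chance of declaring non-inferiority: Φ( (d + 0.07) / se - 1.96 )

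The true difference sits exactly on the margin, so any such declaration is false.

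| x (assumed) | LIBS children removed | LIBS rate | Difference (points) | False non-inferiority |
|---|---|---|---|---|
| 0 | 0 | 60.0% | -7.0 | 2.5% |
| 1% | about 2 | 60.6% | -6.4 | 3.2% |
| 3% | about 5 | 61.9% | -5.1 | 5.3% |
| 5% | about 8 | 63.2% | -3.8 | 8.5% |

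For x = 5%: p = 0.60/0.95 = 0.6316; d = -0.0384; se = 0.0536; (0.0316/0.0536) - 1.96 = -1.37; Φ = 0.085.

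**3. Direction.** The shift depends on imbalance.

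- The same fraction of non-recoverers removed from both arms: d = -0.07/(1 - x), which is wider. At 5%, 0.6316 - 0.7053 = -7.4 points.
- Removed children recovering at their own arm's rate: the difference stays at -7.0.
- 5% non-recoverers removed from CSB+ only: 0.60 - 0.7053 = -10.5 points, against LIBS.

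**4. SAM referral.** Data collection refers the child to a SAM clinic; Outcome variables declares the child a failure; Data analysis keeps the non-cured in the per-protocol set and drops those transferred out. The better reading is failure, hence non-cured, hence kept. The article does not say in terms that this referral is not a transfer out.

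**The case against.** The strongest reply is that the exclusion sentence is safety narrative in a section on benefits, while Data analysis is where the sets are defined, and its ITT set is the right one. That stands in part: a reader might infer that ITT is biased as defined, and it is not. The conflict remains, because field staff will act on the exclusion sentence and the analyst cannot recover an endpoint that was never measured.

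Second, imbalance between arms is not shown. LIBS contains 25 g of peanut, but CSB+ contains soya, the Harms section describes the allergy risk as minimal and the ingredients as already eaten locally, and no comparative rates are given. That stands, which is why the figures above are conditional.

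Three further inferences are tempting and should not be drawn:

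- *That transfers out are linked to the supplement.* Nothing in the article says so, and they leave the per-protocol set only.
- *That SAM referrals are dropped from the per-protocol set.* With assumed referral of 10% on LIBS and 5% on CSB+, 0.60/0.90 - 0.67/0.95 = -3.9 points. Those rates appear nowhere in the article, and its failure definition, read with the retention of non-cured children, points the other way.
- *That the per-protocol set needs a minimum intake because distributors record it* ("they will check for and quantify the amount of supplement consumed by the children"). Keeping non-consumers can dilute a difference. But intake may itself depend on the supplement, so dropping low eaters could remove LIBS failures and favour non-inferiority. It is a trade-off, and a detail an article may leave to the full protocol.

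**Conclusion.** The contradiction between the exclusion rule and the ITT definition is established from the text, as is the absence of any outcome rule for the excluded children. Bias is conditional: it needs the exclusion rule to be followed in a way that removes children or loses their outcomes, and more likely non-recoverers to be lost from LIBS than from CSB+. Under the assumption of LIBS-only removal of non-recoverers at 1% to 5%, about 2 to 8 children, the apparent difference moves by about 0.6 to 3.2 points against a 7-point margin. With equal removal there is no gain for LIBS. The SAM point is a supporting clarification, since the text already leans towards the right answer.

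**What to change.** 1. In Potential benefits, replace the exclusion sentence with one saying that these children, in either arm and whatever is decided clinically about the supplement, remain in follow-up for outcome measurement and in the ITT set. If no outcome can be obtained, they count as not recovered.
2. In Data analysis, add that a child referred for SAM is a failure under Outcome variables, is kept as non-cured in both the ITT and per-protocol sets, and is not counted as transferred out.

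Both should be settled before the data are unblinded. The cost is two sentences and continued measurement of a few children by data collectors who already make weekly visits. The not-recovered rule is a fallback: if missing outcomes fell mainly on CSB+ it would lower the CSB+ rate and help LIBS, so measurement comes first and the number of children to whom the rule was applied should be reported by arm. Neither change touches clinical care.

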### SPIRIT guidelines

The study protocol followed the SPIRIT guidelines for randomized controlled trials.

## Discussion

MAM is a state that needs to be managed before it progresses to the life-threatening condition which is SAM. It is known that SAM has a high contribution to the global morbidity and mortality of young children [2]. Children with MAM need to achieve catch-up growth in weight and height, and they must be able to fight against infection and disease. That is why, currently, specific nutrient recommendations have recently been established for children with MAM living in developing countries [10].

The 2012 WHO technical note on supplementary foods for treating MAM in children aged 6 to 59 months recommends the delivery of locally available, nutritious foods to enhance nutritional status and prevent SAM [4]. It is important to evaluate the effect of feeding acute moderate malnourished children with local ingredient-based supplementary food. The food supplement referred in this paper is LIBS made from locally available ingredients either cultivated locally or found in the local market. If this study demonstrates positive results, it will provide a direction to the public, policymakers and academics, as locally available nutritious foods have the potential to enhance recovery from MAM and reduce the burden of malnutrition. The current study intends to determine the recovery rate from MAM by examining baseline and end-line measurements of MUAC and WHZ scores of the subjects. It will also evaluate the average weight gain and time of recovery.

## Trial status

The trial was registered with the Pan-African Clinical Trial Registry on 11/09/2018 and the trial number is PACTR201809662822990.

## Data Availability

The datasets used and/or analyzed during the current study will be available from the corresponding author, on reasonable request.

## Abbreviations

ANOVA: Analysis of Variance
CSB +: Corn-Soy Blended Flour Plus.
ITT: Intention-to-Treat
LIBS: Local Ingredients Based Supplement
MAM: Moderate Acute Malnutrition
MUAC: Mid-Upper Arm Circumference
PACTR: Pan-African Clinical Trial Registry
PP: Per Protocol
SAM: Severe Acute Malnutrition
SFP: Supplementary Feeding Program
UNICEF: United Nations Children’s Fund
WHO: World Health Organization
WHZ: Weight-for-Height Z-score
